## Abstract

**Introduction:**

Pars plana vitrectomy with intravitreal gas tamponade has been the standard treatment for full-thickness macular holes (FTMHs) for the last 30 years. Gas tamponade has multiple drawbacks: it results in very poor vision for several weeks, limiting patients’ ability to drive and work; many undertake intensive face-down posturing for about a week after surgery, to float the gas bubble onto the macula; gas is cataractogenic and prevents adequate fundus examination; it can elevate intraocular pressure, mandating regular hospital review; patients cannot fly and the fluorocarbon tamponades are extremely potent and long-lived greenhouse gases.

Six uncontrolled retrospective case series have reported promising results utilising novel FTMH surgery without gas tamponade.

The study aims to establish if it is feasible to recruit, retain and evaluate patients with FTMHs into a pivotal randomised control trial of vitrectomy without gas tamponade. The main clinical aim is to collect preliminary safety and efficacy data, comparing gasless with standard vitrectomy.

**Methods and analysis:**

This randomised, assessor-masked, surgical, feasibility study aims to recruit 60 participants with FTMH from six English National Health Service sites. Participants will be randomised 1:1 to either standard vitrectomy, gas tamponade and postoperative posturing, or to gasless vitrectomy without posturing. Gasless surgery involves folding a hinged flap of internal limiting membrane over the hole, secured by gravity and a viscoelastic gel. Participants attend postoperatively for examination and imaging. The main feasibility outcomes are recruitment and retention rates, cross-over and participant treatment acceptability. The main clinical outcomes are primary FTMH closure (3 months), best-corrected visual acuity (6 months) and adverse events.

**Ethics and dissemination:**

South Central–Hampshire A research ethics committee gave a favourable opinion of the study (Reference: 24/SC/0019, 16 February 2024). The study results will be published in a peer-reviewed journal.

**Trial registration number:**

NCT06079593 .

WHAT IS ALREADY KNOWN ON THIS TOPICFull-thickness macular holes can cause severe visual impairment and are currently treated with vitrectomy and gas tamponade. Gas tamponade has risks, and the associated head posturing imposes a burdensome and slow patient recovery.WHAT THIS STUDY ADDSThis is the first randomised controlled trial of macular hole surgery without gas tamponade. It will assess if a pivotal trial is feasible, inform its design and provide early efficacy and safety data.HOW THIS STUDY MIGHT AFFECT RESEARCH, PRACTICE OR POLICYGasless surgery would represent the largest advance in macular hole surgery for 30 years, eliminating the many downsides of gas tamponade.

## Background

Full-thickness macular holes (FTMHs) are anatomical foveal defects of all neuroretinal layers. The resulting central scotoma can cause significant visual impairment.^1^ The annual incidence is approximately 8 per 100 000 per year, with the majority occurring after age 65.^2^,^6^

Introduced in 1991, pars plana vitrectomy (PPV) with gas tamponade is now the standard treatment for FTMHs. PPV is combined with removal of the internal limiting membrane (ILM) in 95% of cases, and virtually all cases have intraocular gas tamponade.^7 8^

Recent meta-analyses reported posturing may not be necessary for FTMHs under 400 µm in diameter, but posturing is associated with improved hole closure in holes larger than 400 µm.^9^,^13^ Even if the benefit of posturing for small holes is questioned, 78% of surgeons advise it nonetheless, as the evidence is hard to interpret.^14^

There are material patient risks and burdens associated with intraocular gas. Gas absorbs spontaneously over about 4–8 weeks, but while present, it obscures vision in the affected eye and impairs binocularity, limiting patients’ ability to judge distances, drive and work.^15^ Macular hole surgery is more urgent than many elective vitreoretinal operations, as the duration of macular hole is one of the key drivers of the visual outcome. The chance of normal (20/25 or better) vision is much higher with very recent onset holes (70.6% vs 29.4%), so these cases should be treated urgently.^16^ Gas is thought to aggravate the development of post-vitrectomy cataract.^17^ Raised intraocular pressure (IOP) occurs in 15.3%–21.1% of cases.^18 19^ Gas dilution errors are rare, but can cause precipitously high IOP. Raised IOP can be painful and cause glaucomatous optic neuropathy and retinal vein occlusion.^20^ Many surgeons bring patients back early, largely to monitor IOP. Patients cannot fly, or have inhaled nitrous oxide anaesthetic until the gas absorbs.^21^ Gas can displace the intraocular lens (IOL) that is inserted during combined cataract-macular hole surgery, leading to pupil abnormalities and altered light sensitivity. Gas also makes it hard to examine the fundus, so hole closure cannot be verified (delaying repeat surgery), and other problems may go undetected.

Postoperative face-down posturing is particularly burdensome for patients.^10^ A typical regimen is face down overnight for the first night, then face down by day for 50 min/hour for 5–7 days. Thus, many patients need a carer postoperatively, many develop musculoskeletal symptoms, and some get deep vein thromboses due to immobility.^22^ Unsurprisingly, up to 50% of patients are poorly compliant with posturing, with 58% reporting that face down posturing with gas was either uncomfortable or very uncomfortable.^23^ All of our study patient involvement group described gas and postoperative posturing as the most difficult aspects of recovery following surgery.

Six recent, proof-of-concept case series reported successful FTMH surgery without the need for either posturing or intraocular gas. In two, an inverted ILM flap covered or filled the hole; the flap was kept in position using viscoelastic or autologous blood as a form of ‘glue’.^24 25^ Two series have subsequently used the viscoelastic technique,^26 27^ and another has used fibrin glue to hold the flap in situ.^28^ The final series completely removed the ILM surrounding the FTMH and used a plug of autologous blood to seal the hole.^29^ Primary closure rate was 80% of 10 patients in the fibrin glue series and ranged from 91.7% to 100% across 98 patients in the other five series, comparing favourably to current surgical success rates.^24^,^29^ The series’ report successful surgery on all sizes of FTMH, and safety was acceptable.

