Those randomised to standard vitrectomy will have the same surgery including a single, approximately 1 disc diameter circular ILM peel centred on the hole, but this will be discarded, and 16% C2F6 tamponade injected into the eye. ILM peeling has been chosen as the single technique for the standard of care arm, as it is still the most common technique in the UK for managing FTMHs.^30^ C_2_F_6_ has been selected as UK practice surveys indicate it is the most commonly used FTMH tamponade.^14^

In both arms, sclerotomies can be sutured if the surgeon deems it necessary.

Surgery will be video recorded (included in consent), and the duration will be recorded for all operations. Both arms will be seen 1 day, 1 week and 1, 3 and 6 months postoperatively.

Repeat surgery with vitrectomy and gas for non-closed holes will be allowed and considered a ‘failure’.

Other surgical steps will be those routinely used by the operating surgeon, or as needed to deal with any complications, such as cryotherapy and gas for a retinal tear.

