#### Safety outcomes

Adverse events (AEs).Intraoperative and postoperative complications.Development or progression of lens opacity within 6 months of vitrectomy (proportion undergoing or listed for cataract surgery and mean change in Lens Opacities Classification System 2 (LOCS2) grading).

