**Figure 1 F1:**
[figure not shown]
Study flow chart. C_2_F_6_, hexafluoroethane; FTMH, full-thickness macular hole; MacTSQ, Macular Disease Treatment Satisfaction Questionnaire; n, number; NEI VFQ-25, National Eye Institute 25-Item Visual Function Questionnaire.

Screening will occur once the participant has given their written informed consent, and surgery defines the baseline visit. Participants will be randomised at the time of screening once the investigator has confirmed eligibility and a decision has been made regarding combined surgery.

Participants will be seen for follow-up according to a typical standard of care, with appointments at day 1, week 1, month 1, month 3 and month 6. A summary of the trial procedures at each appointment is included in table 1.

**Table 1 T1:** Schedule of study assessments, summary of visit activities

Activity	Screening	Baseline	D1	W1	M1	M3	M6
Visit window (±days)	Day −42 to 0	–	0	±3	±7	±7	±7
Consent	X						
Medical and ophthalmic history	X						
Randomisation	X						
Vitrectomy		X					
Full refracted ETDRS BCVA	X					X	X
Clinic ETDRS VA*			X	X	X		
Service user questionnaire (posturing compliance)			X	X			
Macular Disease Treatment Satisfaction Questionnaire			X	X	X	X	X
Visual Function Questionnaire 25-Item	X						X
Slit-lamp examination and IOP	X		X	X	X	X	X
Lens grading	X		X	X	X	X	X
OCT (if possible)†	X		X†	X†	X	X	X
Adverse events (safety)	X	X	X	X	X	X	X
Concomitant medications	X	X	X	X	X	X	X

* Clinic ETDRS VA should be undertaken in the study eye only using an ETDRS chart with correction of any refractive error, with and without. pinhole. This should be undertaken by unmasked assessors at day 1, week 1 and month 1 in both arms. Thereafter from month 3, only suitably trained and delegated masked assessors should undertake Full refracted ETDRS BCVA.

† OCT at the ‘day 1’ and ‘week 1’ visits may not be possible in those receiving gas tamponade and may be omitted at these two visits for participants in the control arm. OCT must be performed in the study eye for all participants at all other visits, and at the day 1 and week 1 visits for those in the novel surgery arm.

BCVA, best-corrected VA; ETDRS, Early Treatment Diabetic Retinopathy Study; IOP, intraocular pressure; OCT, optical coherence tomography; VA, visual acuity; VFQ-25, National Eye Institute 25-Item Visual Function Questionnaire.

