### Statistical methods

#### Statistical methods for primary and secondary outcomes

The proportion of patients who are successfully recruited after screening will be reported with 95% CIs computed by the exact binomial method, as will all outcomes assessing feasibility except for recruitment rate, which will be reported per site per month. In addition to summary statistics of the secondary outcomes (similarly to the primary and baseline outcomes), all harms and withdrawals will be reported with 95% CIs.

An exploratory efficacy analysis will be based on intent-to-treat and include all randomised participants. A secondary analysis will be per protocol comparing those who had gasless vs standard surgery, irrespective of allocation, to investigate the effect of cross-over. The safety population will include all participants who underwent randomisation.

The proportion of participants with primary surgical anatomical closure and mean BCVA (change from baseline, and area under the curve (AUC)) will be compared between groups at 6 months (Fisher’s exact test and Mann-Whitney, respectively). For the AUC analysis, VA will often be below 1 ETDRS letter when gas is in the eye, so ETDRS acuity will be converted to logarithm of the minimum angle of resolution (logMAR) with assignment of logMAR values to count fingers or worse^36^:

Count fingers at 2 ft: logMAR+1.85.

Hand motions at 2 ft: logMAR+2.3.

Visual acuity of ‘light perception’ or ‘no light perception’ will not be converted and will be reported separately.

Adherence to posturing and treatment acceptability will be described.

The MacTSQ has been validated for use in macular diseases requiring drug administration and consists of two subscales: information provision/convenience and treatment satisfaction.^35^ The individual scores from each subscale as well as the composite score will be analysed based on change from the first time point (paired sample t-test) and between groups (analysis of variance model).

Quantifiable findings from the MacTSQ will be analysed using descriptive statistics. Open-ended responses will be analysed for descriptive and analytic accounts using thematic analysis and a constant comparison approach. Analysis will pay particular attention to key factors that impact on patient experiences both positively and negatively and will integrate quantifiable data from the MacTSQ in the analysis to investigate patterns of experience within the participant population.

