### Harms

All AEs will be recorded in the CRF following consent until the patient completes the study.

All serious AEs (SAEs) (except those specified below as not requiring reporting to the Sponsor) must be recorded on an SAE form. The PI or designated individual will complete an SAE form, and it should be emailed to both the King’s College Hospital Research & Development office and to the CI within one working day of the investigator becoming aware of the event.

Reporting of safety, including all AEs, is a secondary outcome. AEs and SAEs will be reported using the Medical Dictionary for Regulatory Activities (MedDRA version 24.0).

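### Early transient retinal and macular adverse events can be found more readily in gasless eyes than in gas-filled eyes, and the stated harms reporting makes no allowance for this

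*Protocol article*

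**What the plan says.** All places are in the protocol article.

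- **Background:** "Gas absorbs spontaneously over about 4–8 weeks". On the consequence for examination: "Gas also makes it hard to examine the fundus, so hole closure cannot be verified (delaying repeat surgery), and other problems may go undetected".
- **Intervention:** "Both arms will be seen 1 day, 1 week and 1, 3 and 6 months postoperatively". Visits are the same in both arms.
- **Table 1, OCT footnote:** at day 1 and week 1, OCT "may be omitted at these two visits for participants in the control arm". It is compulsory "at the day 1 and week 1 visits for those in the novel surgery arm". At every other scheduled OCT visit, month 1 included, it is compulsory for everyone.
- **Who will be blinded?:** gas is expected to be likely still in the eye at day 1, week 1 and month 1.
- **Safety outcomes:** the list includes "Intraoperative and postoperative complications".
- **Harms:** "All AEs will be recorded in the CRF following consent until the patient completes the study". The next section adds that retinal breaks found after surgery count as adverse events.
- **Statistical methods for primary and secondary outcomes:** "all harms and withdrawals will be reported with 95% CIs", in a safety population of everyone randomised.
- **Objectives:** comparing preliminary safety between the two operations is part of the main clinical aim.

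**The concern.** A count of adverse events by arm compares risks fairly only if the arms are searched equally well. Here the search for retinal and macular events is unequal in the first weeks, by schedule (OCT at day 1 and week 1) and by optics (gas in the control eye). The imbalance runs one way. Something seen on an early scan in a gasless eye becomes an adverse event; the same finding in a gas-filled eye may resolve unseen.

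At stake is the descriptive safety comparison. In a feasibility trial of 60 this comparison is the main safety output, and it will inform whether and how a pivotal trial goes ahead. The data monitoring committee also reviews safety at intervals. Interim data hold proportionally more early follow-up, where the imbalance is greatest.

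**Working it through.** **Arm size.** The plan's only size figure is 60 participants with 7% attrition. 60 × 0.93 = 55.8, or about 28 per group, which agrees with the plan. This point does not dispute it. The illustration below uses 60 / 2 = 30 randomised per arm.

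**Compulsory postoperative OCTs by arm (Table 1 and footnote).**

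- Gasless: day 1, week 1, months 1, 3 and 6 = 5.
- Control: months 1, 3 and 6 = 3. Where gas still blocks the view at month 1, 2 are informative.
- Restricted to months 3 and 6: 2 against 2.

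**Which events are affected.** Take an event visible only on fundus view or OCT, with onset at day T and duration D days. It is found if some visit day t with a view satisfies T ≤ t < T + D. Visits are placed at days 1, 7, 30, 90 and 180. Onset and duration are assumptions, because the document gives none.

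Worked case: onset uniform over days 0–30, D = 14.

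- Gasless: onset in days 0–7 is caught at day 1 or 7, and onset in days 16–30 at day 30. (7 + 14)/30 = 70%.
- Control, view at month 1: 14/30 = 47%.
- Control, no view at month 1: every event ends by day 44, before day 90, so 0%.

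| Onset | Duration | Gasless | Control, view from month 1 | Control, view from month 3 |
|---|---|---|---|---|
| Week 1 | 14 days | 100% | 0% | 0% |
| First 30 days | 7 days | 47% | 23% | 0% |
| First 30 days | 14 days | 70% | 47% | 0% |
| First 30 days | 30 or 60 days | 100% | 100% | 0% |
| Any time over 180 days | 14 days | 27% | 23% | 16% |
| Any | Persists to month 6 | 100% | 100% | 100% |

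Control detection is never the higher one. The gap vanishes for persistent events, and for month-long events if the month 1 view is good.

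**Illustrative size.** Let p be the same true risk in both arms and d the detection under gas relative to gasless eyes. The false excess is p(1 − d), or 30p(1 − d) participants.

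- p = 0.10, d = 0: 3 against 0 of 30, 10 percentage points.
- p = 0.10, d = 0.5: 3 against 1.5 of 30, 5 points.
- p = 0.20, d = 0.5: 6 against 3 of 30, 10 points.

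With d = 0.5, a two-sided Fisher test at 5% would be significant in about 2% of trials at p = 0.10 and 10% at p = 0.20. The distortion is thus in the estimate far more than in any test, and the protocol names no between-arm test of harms.

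**The case against.** The strongest reply has four parts.

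1. **The analysis plan is not shown.** The article says a detailed plan was written before recruitment, and splitting harms by visit or detection method could be there. This stands as a caution: the article names neither a single pooled harms table nor a formal contrast, and a reader who infers one goes beyond the text. What remains is that the article itself fixes the unequal OCT schedule and the whole-study recording period. It also adapts to gas elsewhere (unmasked early acuity, conversion of very low acuity for the area under the curve) but not for harms. If visibility is not recorded at the visit, no later analysis plan can fully recover it.

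2. **Gas does not blind the examiner until month 3.** A reader might infer that the control fundus is hidden throughout and can be assessed only at months 3 and 6. The text says it is hard to examine. Absorption takes about 4–8 weeks, and month 1 OCT is required in both arms with a window of ±7 days, so some control eyes may be clear by then. The written OCT difference is two visits.

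3. **Few event types are affected.** Slit-lamp examination, pressure measurement and lens grading follow the same schedule in both arms. Failed closure is not an adverse event unless it means a return to theatre. It would be wrong to say that the comparison of complications as a whole is tilted.

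4. **The size is assumed and within sampling noise.** An exact 95% CI for 3/30 is about 2% to 27%. This is fair, but noise does not cancel a bias whose direction is known in advance, least of all one that costs little to remove.

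**Conclusion.** The concern holds in a limited form. For posterior-segment events that need a fundus view or OCT and resolve before the gas clears, early detection is better in the gasless arm. Part of this is written into the visit schedule, and the stated harms reporting makes no allowance for it. The direction is against gasless surgery. Events still present at month 3 or 6 can be found in both arms, though possibly later in controls; pressure, lens and systemic events are not affected. Gasless participants converted to gas lose the view too, which shrinks the imbalance.

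The size cannot be computed from the document. The 5–10 point range rests on an assumed common risk of 10% and assumed detection of 0–50% under gas; it is an illustration, not an estimate for this trial.

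A reader might also take freedom from safety concerns as a stated condition for going on to a pivotal trial. The Discussion mentions it only within an example, after saying that no single threshold decides and that the results will be weighed together. The point is a worthwhile, cheap improvement to the safety comparison and does not invalidate it.

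**What to change.** Keep the full adverse event table as planned and add one supplementary table, defined before data are seen.

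1. List in advance the event types whose detection needs a fundus view or OCT.
2. For these, compare the arms on findings present at month 3 or month 6. Include any event at any time that caused symptoms or needed treatment, on its own row. That row is not wholly immune, since gas also obscures the patient's vision and treatment follows detection.
3. List incidental earlier findings by visit and arm, using as denominator the number of eyes with a gradable fundus or OCT view at that visit. Record this as a yes/no item, or take it from whether a gradable OCT was obtained. Counting viewable eyes also deals with gasless participants converted to gas.
4. State beside the full table that early posterior-segment findings were not sought equally in the two arms.

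The cost is one extra table and one form item at existing visits. No visit, assessment or treatment changes. Early transient findings drop out of the main comparison for these event types but stay visible in the list and in the full table.

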### Objectives

The study aims to establish if it is feasible to recruit, retain and evaluate patients with FTMHs into a pivotal randomised control trial of vitrectomy without gas tamponade. The main clinical aim is to collect preliminary safety and efficacy data, comparing gasless vitrectomy with standard vitrectomy with gas. The study also hopes to inform future trial design.

## Methods

### Trial design and setting

This is a randomised, two group, 1:1 allocated, active-control, multicentre, assessor-masked, surgical feasibility trial of approximately 36 months. Participants will be recruited and treated from approximately six National Health Service (NHS) teaching hospitals in England. The trial assesses a new surgical technique. Surgery uses an intraoperative viscoelastic, licensed as an ophthalmic viscosurgical device (OVD) and used within the scope of its indication for use. Therefore, from a UK regulatory perspective, this is not a Clinical Trial of an Investigational Medical Product.

As sites are selected, details will be available on the study record on ClinicalTrials.gov.

### Eligibility criteria

Eligibility criteria will be assessed by study ophthalmologists at participating sites based on the following criteria:

#### Inclusion criteria

Requiring PPV to treat idiopathic (primary) FTMH.18 years or older.Early Treatment Diabetic Retinopathy Study (ETDRS) best-corrected visual acuity (BCVA) letter score of 1 or better in the study eye.Able to provide written informed consent.

#### Exclusion criteria

General:

Hypersensitivity to hyaluronate or other components of Healon Pro viscoelastic.Any major illness or major surgical procedure within 4 weeks.Any other condition that, in the opinion of the investigator, would prevent the participant from granting informed consent or complying with the protocol.

Study eye

Previous vitreoretinal surgery, retinopexy, open-globe injury or endophthalmitis.Presence of fibrotic retinal proliferation or central epiretinal membrane (within 1 disc diameter of the fovea).Aphakia.Current or former myopia greater than 6 dioptres.Current or previous posterior uveitis or choroiditis.Presence of other ocular comorbidity that, in the opinion of the investigator, is likely to impair BCVA postoperatively or affect FTMH closure.Current ocular or periocular infection, other than mild or moderate blepharitis.Lens or media opacity that precludes adequate retinal assessment and imaging.

